### Clinical assessments

Clinical assessments are standardised and recorded on the existing skin assessment database used for school health clinics. A written description of the location of the lesions and identification of the primary lesion being used for assessment is recorded. A paper template is also provided to allow nurses the option to mark on a diagram the location of the lesions.

Seven days after commencing the trial (day 7), the participant is re-assessed by the school nurse, who also records whether the lesion has improved. Both child and caregiver are asked to comment on their satisfaction with treatment and any adverse events related to the medication, including itch, pain, or allergy. School records are checked for absence over the prior 7 days.

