### Intervention

All lesions are cleaned with saline and scabs gently removed. For the group randomised to fusidic acid, 2% fusidic acid ointment (DP Fusidic Acid, Douglas Pharmaceuticals Ltd, Auckland, NZ) is applied topically, and for the hydrogen peroxide arm, 1% hydrogen peroxide cream (Crystaderm, AFT Pharmaceuticals, Auckland, NZ) is applied topically. In both cases, an adequate amount to cover each lesion is used and dressing(s) then applied. A tube of appropriate topical medication is supplied for the child and/or caregivers to continue applications twice daily for 5 days with dressing changes. Participants allocated to simple hygiene measures receive no medication but a dressing is applied following the cleaning of the lesion(s). All participants are provided with supplies to allow them to clean and redress the wound twice daily for 5 days. Low adherent wound pads are used so as not to interfere with the wound healing process. In all groups, scabies is treated if present.

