### Harms

Any adverse event will be reported; these are defined as any untoward medical occurrence in a subject without regard to the possibility of a causal relationship after entry into the study and until the completion of the study. At day 2 and day 7 of the trial, a safety check is performed by the school nurse to assess for rapid worsening of the impetigo or for adverse effects. If these occur, then the participant can be withdrawn from the trial at the discretion of the nurse. On day 2 and day 7, participants and/or caregivers are directly questioned regarding specific harms including itch, pain, redness, or any other adverse effects of medication. Any requirement for additional medical intervention is considered a potential harm. All harms will be reported.

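### Day-7 and open-ended harms questions are tied to medication, which one arm does not receive, so they conflict with the protocol's cause-free adverse event definition and risk under-reporting in simple care

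*Protocol article*

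**What the plan says.** Five statements in the protocol article bear on this point.

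- **Definition (Harms).** Adverse events are "any untoward medical occurrence in a subject without regard to the possibility of a causal relationship", from study entry to completion, and all harms are to be reported.
- **Day-7 question (Clinical assessments).** Child and caregiver comment on "any adverse events related to the medication, including itch, pain, or allergy".
- **Direct questioning at days 2 and 7 (Harms).** Families are asked about "specific harms including itch, pain, redness, or any other adverse effects of medication". The same section describes "a safety check is performed by the school nurse to assess for rapid worsening of the impetigo or for adverse effects" and treats a need for further medical intervention as a potential harm.
- **The third arm (Intervention).** "Participants allocated to simple hygiene measures receive no medication"; they have the lesion cleaned and dressed.
- **Use of the data.** Secondary outcomes lists a comparison of adverse events between the arms. The section on allocation concealment says that participant and nurse both know the allocation.

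**The concern.** The definition ignores cause, but both descriptions of what families are asked bring cause back in. Clinical assessments does so for the whole question. Harms does so for the part that should catch anything not named.

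The restriction does not fall equally on the arms. In the two cream arms a question about effects of medication has an obvious referent. In simple care it has none, and both the person answering and the person recording know that. A family whose child had a reaction to the dressing, or some unrelated problem, could reasonably answer that there was no effect of medication. The same event in a cream arm could well be mentioned.

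At stake is the between-arm comparison of adverse events, a secondary outcome. Any shortfall would favour simple care over both creams. An event never elicited cannot be recovered at the analysis stage.

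**Working it through.** The protocol gives no figure on this point, so the check is mainly a comparison of its sections.

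**1. Definition against question.** The definition in Harms is independent of cause. The day-7 question in Clinical assessments is restricted by cause. The two do not agree.

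**2. The open-ended question in Harms.** Its named items (itch, pain, redness) stand on their own and can be asked in any arm. Its residual item is tied to medication. The conflict therefore also exists within Harms, but only for events that are not named.

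**3. What is covered in every arm.**

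| Type of event | How it is elicited | Depends on having a medication? |
|---|---|---|
| Itch, pain, redness | Named prompts, days 2 and 7 (Harms) | No |
| Worsening of the impetigo | Nurse check, days 2 and 7 (Harms); caregivers asked to contact the nurse between visits (Participant timeline) | No |
| Event needing further medical care | Counted as a potential harm (Harms) | No |
| Allergy | Named at day 7 only, as related to the medication (Clinical assessments) | Yes, as worded |
| Any other event | Residual item (Harms); day-7 question (Clinical assessments) | Yes, as worded |

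The nurse check also covers adverse effects in general, which gives some protection to the last two rows. The exposure lies mainly in those rows.

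**4. Size, as an illustration only.** Let p be the true rate of such events, equal in all arms, and let s be the fraction that simple care reports relative to a cream arm. Neither is in the documents; both are assumptions. The number per arm is n = 160, the evaluable number in Sample size.

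- Recorded rates: p in a cream arm, q = p × s in simple care. False difference: d = p − q.
- Chance of two-sided p<0.05 = Φ[(d − 1.96 × SE0) / SE1], where SE0 = √(2 × m × (1 − m) / n), m = (p + q)/2, and SE1 = √([p(1 − p) + q(1 − q)] / n).

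Worked case, p = 0.10 and s = 0.5: q = 0.05, d = 0.05, m = 0.075.

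- SE0 = √(2 × 0.075 × 0.925 / 160) = 0.0295
- SE1 = √((0.09 + 0.0475) / 160) = 0.0293
- (0.05 − 1.96 × 0.0295) / 0.0293 ≈ −0.26, so the chance is about 40%.

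| True rate p | s = 0.75 | s = 0.50 | s = 0.25 |
|---|---|---|---|
| 5% | 1.25 points, 8% | 2.5 points, 22% | 3.75 points, 49% |
| 10% | 2.5 points, 12% | 5 points, 40% | 7.5 points, 79% |
| 20% | 5 points, 22% | 10 points, 71% | 15 points, 98% |

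Each cell gives the false difference and the chance of p<0.05 for one cream arm against simple care. With s = 1 the difference is zero and that chance is the nominal 5%.

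**The case against.** The strongest reply has four parts.

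- **Families are not asked only about medication effects.** This stands. The prompts for itch, pain and redness, the nurse check and the counting of further medical care carry no restriction by arm. A reader might infer that the comparison is biased by construction, or that itch, pain or spread in simple care is what would be missed. The documents do not support either: those are the events with the most cover.
- **The article uses medication loosely.** The section on the primary outcome speaks of discontinuing trial medication, although that outcome applies to all three arms. The word may simply mean assigned treatment, and nowhere is the question said to be skipped in simple care. This is a fair reading and lowers the likely size of the problem. It does not remove the ambiguity for the nurse who puts the question or the family that answers it.
- **The questionnaire is not shown.** The article may paraphrase a better-worded script. True, so the finding is limited to the wording as published, and that wording contradicts the definition.
- **The prompt lists differ only in drafting.** Both lists are illustrative, so redness in one and allergy in the other is not a contradiction in itself. This stands; it is a reason to align them, no more.

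A reader might also infer that itch, pain and redness are not recorded at baseline, so that persisting disease cannot be told from a treatment effect. The section on demographic characteristics lists what will be reported, not the whole data form, so their absence there shows nothing. Randomisation also balances such symptoms in expectation.

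**Conclusion.** The concern holds in a limited form. The protocol's stated questions about harms are narrower than its own definition of an adverse event, and the part that is narrower has no natural referent in the arm without medication. With unblinded reporting and recording, this creates a risk that events outside the named prompts are under-reported in simple care, in that arm's favour.

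It is a risk and not a demonstrated bias. Its size depends on the true rate of unprompted events and on the relative reporting fraction, and the documents give neither. Over the assumed ranges above, the false difference runs from about 1 to 15 points; with equal elicitation it is nil. A calculation that sets reporting in simple care to zero would not be a fair guide, given the direct questioning in every arm.

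The matter concerns a secondary safety outcome and leaves the primary analysis untouched. It should still be corrected, because the remedy is cheap and lost reports cannot be restored later.

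**What to change.** Reconcile Clinical assessments with Harms by adopting one arm-neutral script, used word for word in all three arms at day 2 and day 7:

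- the same prompted items each time (itch, pain, redness, allergy or rash, new lesions);
- a closing question on any other new problem since the last visit, whatever the cause;
- relatedness recorded separately, and to the assigned care, including cleaning and dressing, rather than to medication.

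If the questionnaire in use is already worded this way, correcting the two sections of the article is enough.

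The cost is a rewording of the questionnaire and of the matching fields in the electronic database, to which trial questions have already been added. Visits become slightly longer, and more events will be reported in every arm. Recording itch, pain and redness at day 0 would help to separate new symptoms from existing disease. That is an optional extra and does not correct an error shown in the document.

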### Microbiology

All children have a bacteriological dry cotton swab taken from the most severe lesion at presentation and at day 7. Swabs are cultured onto blood agar and any clinically significant growth is reported. The European Committee on Antimicrobial Susceptibility Testing (EUCAST) susceptibility method and criteria are used for *S. aureus* susceptibility testing. Susceptibility is tested to commonly used skin and soft tissue antimicrobials; fusidic acid, flucloxacillin, erythromycin, clindamycin, and co-trimoxazole. If MRSA is identified then extended susceptibility is performed, including mupirocin and tetracyclines. No susceptibility testing is performed on *S. pyogenes*.

## Outcomes

### Primary outcome

The primary outcome of this trial is treatment success assessed by comparison of digital photographs or clinical deterioration based either on digital images or on nursing assessment leading to discontinuing trial medication.

### Secondary outcomes

Clinical success will be compared between groups. This will be defined by
Nursing opinion that the impetigo has improved at day 7Participant and/or caregiver opinion that the impetigo has improved at day 7Microbiological secondary outcomes are eradication of *S. pyogenes* and/or *S. aureus* on day 7 and development of antibiotic resistance on day 7 compared to baselineEducational impact is assessed by comparison of school absence over the 7 days of the trial periodAdverse events will be compared across study arms

### Retention

A supermarket voucher worth NZ$20 ise offered to the family as *koha*, a thank you gift on successful completion of the trial protocol.

### Data management

Trial data is stored using a study identification number on a password protected access database maintained on a secure network. This database is also used to randomise images and presents anonymised pairs of photographs to the graders for analysis, and records the outcomes of the grading.

### Statistical analyses

For baseline data, d**i**chotomous variables will be summarised as proportions of patients in each treatment group, differences between groups will be assessed using a chi-square statistic, and where small cell sizes (less than 5) are present, a Fisher’s exact test will be used. Continuous variables with an underlying normal distribution will be summarised as mean and standard deviation, and differences between groups will be assessed using Student’s *t*-test. Other distributions will be either transformed if suitable and *t*-tests performed with reporting of geometric means or distributions will be reported as median and interquartile range and differences in groups assessed using Wilcoxon rank non-parametric tests with Hodges-Lehmann estimates and 95% confidence intervals.

Analysis will be performed after completion of recruitment. Both hydrogen peroxide and simple hygiene groups will be compared independently with fusidic acid with 95% confidence interval. Non-inferiority will be defined as a treatment success rate of no more than 10% below that of the fusidic acid success rate. An intention to treat and per protocol analysis will be performed using all patients with available primary outcome data. Patients without primary outcome data or for whom caregivers withdrew consent to participate will not be included in the analysis.

To investigate predictors of treatment success, backwards stepwise random-effects logistic regression will be performed on a priori and other variables identified as different in baseline characteristics between randomisation groups.

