### Sample size

On the assumption of non-inferiority between hygiene measures and topical fusidic acid and between topical hydrogen peroxide and fusidic acid, and a predicted efficacy of fusidic acid of 80%, we require 160 patients in each intervention group. This provides 80% power and a one-sided *α* of 0·05 to show non-inferiority (10% margin) between each group and topical fusidic acid. In order to allow for 10% loss to follow-up and subsequent exclusions, recruitment of 178 participants to each group is required. Subsequent exclusions and loss to follow-up are defined as participants not available for follow-up at day 7 or when two digital images are not available to assess. Estimates of efficacy are extrapolated from published data [6, 19, 20], and the 10% margin was considered a clinically significant difference [21].

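### The design uses one-sided alpha 0.05, the analysis names a 95% interval of unstated sidedness and no deciding limit, and neither reading gives the stated 80% power

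*Protocol article*

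**What the plan says.** The Sample size section of the protocol article fixes the design error rate and power: "This provides 80% power and a one-sided" alpha of "0·05 to show non-inferiority (10% margin) between each group and topical fusidic acid". The inputs are "a predicted efficacy of fusidic acid of 80%, we require 160 patients in each intervention group", and recruitment is then raised for loss: "In order to allow for 10% loss to follow-up and subsequent exclusions, recruitment of 178 participants to each group is required".

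The Statistical analyses section describes the comparison: "Both hydrogen peroxide and simple hygiene groups will be compared independently with fusidic acid with 95% confidence interval". The next sentence gives the criterion: "Non-inferiority will be defined as a treatment success rate of no more than 10% below that of the fusidic acid success rate". No sentence says whether the interval is one-sided or two-sided, which limit is compared with the margin, or how the interval relates to the design alpha.

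**The concern.** A one-sided 0.05 non-inferiority test is equivalent to checking the lower limit of a two-sided 90% interval. An ordinary two-sided 95% interval is a one-sided 0.025 test. On the conventional reading, then, the trial is sized for one test and analysed with another, and the only definition of non-inferiority in the article does not say which limit decides.

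The primary conclusion for each alternative treatment could turn on this. Take 128/160 successes on fusidic acid and 125/160 on an alternative. The lower limit of the two-sided 90% interval is -9.4 points, which meets the margin. The lower limit of the two-sided 95% interval is -10.8 points, which does not. If the rule is left open until the data are seen, the choice can follow the result.

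**Working it through.** **Inputs (Sample size section).** Fusidic acid success 80%; margin 10%, taken as 10 percentage points; one-sided alpha 0.05; power 80%; 160 evaluable per arm. No separate rate is given for the alternatives. The section says only "On the assumption of non-inferiority between hygiene measures and topical fusidic acid and between topical hydrogen peroxide and fusidic acid", which I take as 80% in those arms too (true difference zero).

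**Step 1: reproduce the stated sample size.** With equal success p in both arms and margin m:

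n = 2p(1 - p)(z_alpha + z_power)² / m²

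- One-sided 0.05: n = 0.32 × (1.645 + 0.842)² / 0.01 = 197.8, so **198** per arm.
- One-sided 0.025: n = 0.32 × (1.960 + 0.842)² / 0.01 = 251.2, so **252** per arm.

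The stated 160 is not reproduced under either. Other methods with the stated inputs do not give it: Farrington-Manning variance 201, continuity correction 218, log risk ratio 174, arcsine 230, log odds ratio 267. Values near 160 need inputs that the article does not state, for example 85% success in both arms (158) or 81% in the alternative arm (161). The loss adjustment does reproduce: 160 / 0.9 = 177.8, so 178.

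**Step 2: power at 160 per arm.** The standard error of the difference is √(0.32 / 160) = 0.0447, and the margin divided by it is 0.10 / 0.0447 = 2.236.

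- One-sided 0.05 (two-sided 90% interval): Φ(2.236 - 1.645) = **72.3%**.
- One-sided 0.025 (two-sided 95% interval): Φ(2.236 - 1.960) = **60.9%**.

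Exact binomial enumeration with Wald intervals gives 72.4% and 60.9%.

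**Step 3: split the shortfall from 80%.**

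- 80% to about 72%: about 8 points, because 160 does not follow from the stated inputs.
- About 72% to 61%: about 11 points, from deciding on a two-sided 95% interval instead of the design alpha.

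**Step 4: false claims at the margin.** Exact enumeration at 80% against 70% success, 160 per arm:

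- Lower limit of the two-sided 95% interval: 2.6%.
- Lower limit of the two-sided 90% interval: 5.1%.

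**Step 5: how often the two interval rules disagree.** At this standard error they part when the observed difference lies between -10 + 1.645 × 4.47 = -2.6 points and -10 + 1.960 × 4.47 = -1.2 points. With equal true success rates this happens in about 11% of trials, the difference between the two powers in Step 2.

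**Sensitivity.** If true success were 85% in both arms, which the article does not state, 160 per arm would give 80.5% power at one-sided 0.05 but 70.7% with the two-sided 95% interval. The mismatch would still matter.

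**The case against.** The interval sentence does not say two-sided. A one-sided 95% bound would agree exactly with the design alpha, so it goes too far to say that the two sections certainly describe different tests. That stands as a caution. But the two-sided meaning is the conventional one, the same section uses 95% confidence intervals in the ordinary way for baseline comparisons, and nothing in the article resolves the point. Even if a one-sided bound was meant, power is about 72%, not 80%.

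The two-sided 95% interval is also the stricter choice, so this divergence cannot add false claims of non-inferiority. That stands too: the cost is a greater chance of an inconclusive trial.

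A separate analysis plan may exist and may name the deciding limit. The point here is not that omission. It is that the article gives an alpha and an interval that conventionally do not match, and a power that neither delivers.

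A reader might infer three stronger things that the article does not support:

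- **That non-inferiority will be judged on observed rates with no error control.** Applied literally to observed rates, the criterion would give about a 53% false-claim rate at a true 10-point deficit. But it directly follows the interval sentence, and the Sample size section gives an alpha and a margin, which presuppose a formal test. Loose wording is the more likely explanation.
- **That the margin may be relative.** The Sample size section says that "the 10% margin was considered a clinically significant difference", which is ordinary language for an absolute difference. A relative 10% (8 points) would need 310 per arm, further still from 160.
- **That the mismatch explains the whole loss of power.** It explains only the drop from about 72% to 61%.

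**Conclusion.** The concern holds in a limited form. The design alpha and the analysis interval do not match on the conventional reading, and the article does not name the limit that decides non-inferiority. At 160 evaluable per arm, power is about 61% with a two-sided 95% interval and about 72% with the one-sided 0.05 bound; the stated 80% is reached under neither. About 11 points of the gap come from the mismatch and about 8 from a sample size that the stated inputs do not support. These figures assume 80% true success in both arms, an absolute 10-point margin and complete data on 160 per arm.

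**What to change.** State one rule, in the same terms, in the Sample size and Statistical analyses sections: non-inferiority is concluded if the lower limit of the named interval for the difference in success proportions (alternative minus fusidic acid) lies above -10 percentage points. Name the interval and give the matching alpha, then restate power at 160 evaluable per arm:

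- two-sided 95% interval, one-sided alpha 0.025: about 61%; or
- two-sided 90% interval, one-sided alpha 0.05: about 72%.

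Power has to be restated in either case; aligning the interval with alpha 0.05 alone would leave the 80% uncorrected. If 160 rests on a success rate other than 80%, state that rate and recalculate.

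The text change is a few sentences, to be made before unblinding, and its cost is a less favourable stated power. Restoring 80% power is a separate decision. It would need 198 evaluable per arm (198 / 0.9 = 220 recruited, 660 in total) at one-sided 0.05, or 252 (252 / 0.9 = 280 recruited, 840 in total) at one-sided 0.025, against 3 × 178 = 534 now planned.

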## Data collection methods

### Demographic characteristics

Baseline characteristics of participants are collected at the time of randomisation and reported per randomisation group. The following demographic characteristics will be reported: age, gender, ethnicity, weight, history of pre-existing skin disease, allergies, and location of most severe lesion. All data is collected directly onto an electronic database used by school health clinics; additional trial questions have been created and added to this database by the study investigators. An equivalent paper proforma was designed by SP and included in the study materials for use if required.

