### Primary outcome methods

The primary outcome of this trial is treatment success based on comparison of digital photographs taken at days 0 and 7. If clinical assessment leads to early discontinuation of the trial medication, this is also considered unsuccessful treatment. To aid standardisation, the primary outcome uses digital photographs independently assessed by blinded reviewers. The single largest lesion is photographed prior to commencing treatment, using a digital camera at a distance of 15 cm with an adhesive paper tape measure and unique study ID placed next to the lesion. Three digital images are taken at each data collection visit, and all are submitted to the study investigators. The single best quality image is then selected by the lead investigator (SP) for outcome assessment. Pairs of images are presented to three individual assessors blinded to intervention arm. The method of image presentation is randomised such that assessors are unaware of which image was taken first and which second. The outcome will be treatment success if the images are considered healed or improved and treatment failure if they are the same or worse, or if the reviewers cannot determine the outcome based on the digital images (e.g. due to poor quality images). Where there is discordance between assessor opinions, the majority opinion of two out of three reviewers will be considered the correct assessment. Patients removed from the trial protocol by school nurses or general practitioners before 7 days due to clinical deterioration will also be considered treatment failures. This process has been standardised previously in another large RCT of treatment of impetigo in remote access locations; different from our multicentre urban setting [21].

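### The primary non-inferiority comparison names no child-level baseline covariate; pre-specified adjustment could narrow its interval if the collected values are prognostic, but would not by itself restore 80% power

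*Protocol article*

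**What the plan says.** The Statistical analyses section gives the primary comparison in one sentence: "Both hydrogen peroxide and simple hygiene groups will be compared independently with fusidic acid with 95% confidence interval". It then sets the criterion: "Non-inferiority will be defined as a treatment success rate of no more than 10% below that of the fusidic acid success rate". No estimator, model or covariate is named for this comparison.

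The same section does give baseline variables a role, but a different one. Under the aim "To investigate predictors of treatment success" it plans a backwards stepwise random-effects logistic regression. The candidate variables are some chosen a priori and others found to differ between the randomised groups at baseline.

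The values exist before treatment starts. The Demographic characteristics section says: "The following demographic characteristics will be reported: age, gender, ethnicity, weight, history of pre-existing skin disease, allergies, and location of most severe lesion". The Participant timeline section places the demographic data, the photograph and the swab on day 0, ahead of randomisation. Under Primary outcome methods, each photograph is taken "with an adhesive paper tape measure and unique study ID placed next to the lesion".

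**The concern.** The lower confidence limit of the risk difference decides non-inferiority, so its width bears directly on the chance of a conclusive result. In a randomised trial, adjusting for prognostic baseline values narrows that interval and allows for chance imbalance between arms. If the result is expressed as a marginal risk difference, the target of estimation and the 10-point margin stay the same.

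The planned stepwise model cannot do this job. Its variables are chosen partly by observed imbalance and by the stepwise procedure, not fixed in advance. Its natural output is an odds ratio, which cannot be set against an absolute margin.

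Precision matters more than usual here because, on the protocol's own inputs, 160 per group gives less than the stated power.

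**Working it through.** **Inputs.** From Sample size: "a predicted efficacy of fusidic acid of 80%, we require 160 patients in each intervention group". The same success rate is taken in the comparator arms, because no other rate is given and the section begins "On the assumption of non-inferiority between hygiene measures and topical fusidic acid". It continues "This provides 80% power and a one-sided" alpha of 0.05. The margin is 10 percentage points. If the 95% interval under Statistical analyses is two-sided, its lower limit corresponds to one-sided 0.025, so both levels are shown.

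**The plan's own figure.** n per group = 2 × 0.8 × 0.2 × (1.645 + 0.842)² / 0.10² = 197.8, so 198, not 160. At one-sided 0.025 it is 251.2, so 252. A success rate of 85% in both arms would give 158, and 81% in the comparator arm would give 161, but neither is a stated input. The loss allowance does reproduce: 160 / 0.90 = 178.

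**Power without covariates.** SE = √(2 × 0.8 × 0.2 / 160) = 0.0447.
- One-sided 0.05: Φ(0.10/0.0447 − 1.645) = Φ(0.591) = 72.3%.
- One-sided 0.025: Φ(0.10/0.0447 − 1.960) = Φ(0.276) = 60.9%.

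**Power with adjustment.** Let R² be the share of outcome variance explained by the baseline values. As an approximation, the variance of the risk difference is multiplied by (1 − R²), so

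power = Φ(0.10 / √(0.32 × (1 − R²) / 160) − z).

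The documents give no R². The range below is an assumption. The last column is 160 / (1 − R²), the size of an unadjusted trial with the same precision.

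| R² (assumed) | Power, one-sided 0.05 | Power, one-sided 0.025 | Half-width of 95% interval (points) | Equivalent n per group |
|---|---|---|---|---|
| 0 | 72.3% | 60.9% | 8.77 | 160 |
| 2% | 73.0% | 61.7% | 8.68 | 163 |
| 5% | 74.2% | 63.1% | 8.54 | 168 |
| 10% | 76.2% | 65.4% | 8.32 | 178 |
| 15% | 78.2% | 67.9% | 8.08 | 188 |

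**R² needed for 80% power with 160 per group.**
- One-sided 0.05: 1 − 160/197.8 = 0.19.
- One-sided 0.025: 1 − 160/251.2 = 0.36.

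For a normally distributed baseline score in a logistic model with 80% success, R² of 0.19 corresponds to an area under the ROC curve of about 0.79. Both values lie above the assumed range.

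**The case against.** The case against has four parts.

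- **Analysis-plan detail.** The covariate list and the estimator are commonly left to the analysis plan, which is not shown. A reader might infer that the trial has chosen an unadjusted analysis. The text does not say so; it only names no covariate. What remains is that the article does assign baseline variables a place, and that place is outside the primary comparison.
- **No error.** A reader might infer that leaving covariates out makes the primary result wrong or biased. It does not. An unadjusted difference in proportions is valid in a randomised trial. This is a gain in efficiency, not the correction of a mistake.
- **Unknown prognostic strength.** A reader might infer that the interval is certainly too wide. The protocol plans to investigate predictors and reports none. The outcome is a relative grading of paired photographs, and pairs that graders cannot judge count as failures; nothing in the protocol suggests that age or skin history predicts that component. R² near zero is compatible with the documents, and the gain would then be near zero. This objection stands and makes the point conditional.
- **Data not clearly recorded.** Lesion number is only implied by the exclusion of children with more than 3 lesions. Lesion size would have to be newly read from the photographs, with no measurement method defined. This also stands, and it limits the covariates to those already listed.

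How school, the randomisation stratum, enters the analysis is a separate question not dealt with here.

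**Conclusion.** The point holds as a modest, conditional improvement. The primary comparison as written names no child-level baseline covariate, and the only model that uses such values does not serve a margin on the risk difference.

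Over an assumed R² of 0 to 15%, adjustment adds between nothing and 5.9 points of power at one-sided 0.05 (78.2 − 72.3), or between nothing and 7.0 points at one-sided 0.025 (67.9 − 60.9). The figures rest on 80% success in every arm, 160 evaluable children per group and the variance approximation shown.

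A reader might infer that adjustment would rescue the stated 80% power. The figures do not support that. The shortfall arises because 160 per group does not follow from the stated inputs, and it is larger if the 95% interval is two-sided. Both need their own correction.

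**What to change.** Before unblinding, define the primary estimate for each comparison with fusidic acid as the standardised (marginal) risk difference, with its 95% confidence interval. Obtain it from a logistic model with treatment and a short list of covariates fixed in advance from those under Demographic characteristics: for example age, history of pre-existing skin disease and location of the index lesion. Compare the lower limit with -10 points. Keep the unadjusted difference as a supportive analysis, and leave the stepwise predictor model as a separate exploratory one.

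Add lesion number or lesion size only if they are already recorded in the database.

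The cost is a few lines of analysis-plan wording and slightly more analysis work. No additional children, visits or measurements are needed. The gain may prove negligible.
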